### Randomisation, stratification and blinding

Randomisation to the intervention group receiving the MIS or the control group takes place on the level of departments to avoid contamination between health care workers receiving the MIS or not. Prestratification was performed based on two criteria, creating four groups: workers have contact with patient (material) versus workers have no contact with patient (material); and high vs. low risk for developing hand eczema, assessed by the occupational physician. Based on the sequence of inclusion, randomisation was performed in strata of two by an independent researcher. For practical reasons the randomization will be performed before baseline measurements. Workers are not informed about the outcome of the randomisation and the design of the study i.e. the existence of the two groups (control and intervention). The department managers are explicitly requested not to inform their workers about this. It is impossible to blind researchers, occupational nurses and department managers for the intervention.

### Control intervention

The workers in the control group receive a leaflet containing the evidence-based recommendations derived from the NVAB-guideline to prevent and reduce hand eczema.

### MIS intervention

The intervention group receives the multifaceted implementation strategy which consist of participatory working groups combined with a role model training and an educational program including reminders. They also receive the same leaflet as the control group.

The time path of the intervention can be seen in Figure 1.

**Figure 1 F1:**

**Time path of the intervention**.

#### The participatory working groups

The central part of the intervention are the working groups. The goal of the working group is to identify problems with adherence to the recommendations, to find solutions for these problems and implement these solutions at the department. During three meetings, the working group follows seven steps to accomplish this goal. It is expected that approximately 30 working groups are formed in this study, i.e. 10 working groups per participating hospital.

At each department - consisting of approximately 50 workers - one working group is formed. If a department is larger than 50 workers, more workers are asked to be a part of the working group. The members of the working group are selected by the department manager based on representativeness, their influence on colleagues and their motivation.

Each working group consists of a maximum of eight members. Each member has his/her own task during the meetings. The following persons are included in the working group:

• 3 - 5 representative workers: to identify problems with adherence to the recommendations derived from the NVAB-guideline and to come up with solutions to overcome these problems.

• The manager of the department: to judge whether the developed solutions are realistic and achievable, from both financial and organisational points of view

• A person from the infection control department: to judge whether the solutions are in line with the hand hygiene procedures of the hospital

The working group will be guided by a trained occupational nurse. This occupational nurse received a special training before the start of the study. This training focused on both the theory of (the prevention of) hand eczema as well as on the practical aspects of the intervention.

After a working group is formed the researchers plan three meetings. In case a member of the working group is unable to participate, the department manager selects and asks another worker to participate. If the department manager him/herself is unable to participate, a representative is asked to take his/her place.

The programme of the working group consists of the following seven steps:

#### Step 1 Introduction and inventory of the workplace

At step 1 the working group meets for the first time, approximately one month after the baseline measurement. The trained occupational nurse gives information about the study and about the need for the prevention of hand eczema. After the meeting, the participants and the trained nurse conduct four workplace observations. The goal of these observations is to give the participants insight in their risk behaviour related to hand eczema and to identify possible barriers related to the implementation of the recommendations. The following observations are performed:

• Two participants count how many times they wash their hands, use hand alcohol, use skin care products, and use gloves during the day. They receive a counter for this purpose. Each activity is counted during another day.

• One participant places a flap-over in the lunch room of the department. During a meeting or break the participant asks her colleagues to write down the problems they face with adherence to the recommendations.

• The department manager gives a short questionnaire to key-figures of the department - who do not participate in the working group - containing questions about hand eczema and adherence to the recommendations.

• The trained nurse visits the department and pays attention to adherence to the recommendations, relevant exposures, work organization, wet work, deliverance of work (by others), collaborations with others, instructions, skills, materials and equipment.

The researcher analyses the baseline measurement per department and forms - together with the observations - a document for potential obstacles to adhere/implement the guideline. This document is send to the trained nurse and the participants of the working group before the start of the second meeting.

#### Step 2 Collecting problems with adherence

Under guidance of the trained nurse, the second meeting takes place one month after the first. The meeting starts with a presentation of the document on the workplace observations and baseline characteristics. Problems with adherence to the recommendations are derived from this document and presented to the participants. In addition, the participants brainstorm to collect additional problems with or obstacles to adherence to skin protection measures, using post-its according to the nominal group technique [31]. All mentioned problems/obstacles are prioritized according to severity and frequency of the problem both measured on a 4-point Likert scale (not severe - very severe; not frequent - very frequent). The most frequent and severe problems with adherence are written down on a flap-over. Next, each member can chose three problems he/she finds the most important obstacle for adherence to the guideline by adding a sticker. On the basis of consensus, the three problems with the highest number of stickers are considered to be the three most important obstacles/problems considering adherence to the recommendations.

#### Step 3 Collecting solutions

After the three most important problems are chosen, the working group brainstorms about solutions to overcome these problems using again the nominal group technique. The solutions gathered are prioritized according to criteria of existence, feasibility, complexity and the solving capability of the solution. The manager judges whether the costs of the solutions are feasible; the person from the infection prevention department decides whether the solutions are in line with the hand hygiene procedures. The solutions are prioritized using the same method as in step 2, resulting in a top three of solutions.

#### Step 4 Preparing the implementation

The working group prepares a plan for implementation based on the three most important problems/obstacles and their solutions. The plan describes who is responsible for the implementation of the solutions; what type of activities will be performed by whom, how and when; and whether a test phase is needed. Solutions are divided into either short-term (< 3 months) or long-term solutions (> 3 months). The implementation plan is send to all participants of the working group.

#### Step 5 Implementation of the solutions

The members of the working group implement the solutions, supported by the trained nurse. This implementation phase takes place between meeting two and three. To improve the effectiveness of the implementation process, role models are introduced named Dermacoaches. Dermacoaches are workers from the working group who followed a special training about (the prevention of) hand eczema and are trained on how to promote and enhance the implementation of the solutions and adherence to the guidelines. The Dermacoaches stimulate and motivate their colleagues to be aware of their risk behaviour during work and try to decrease the problems with adherence to the recommendations at the department. They also receive a Dermacoach toolkit which contains posters. These posters are used as reminders to the recommendations for their colleagues at the department and are placed at sinks or other relevant places [26]. Other contents of the toolkit are posters and e-mails with the top-3 problems and solutions prioritized by the working group; and presentations on hand eczema, which they can use during work meetings. Further, the role model assists the trained occupational nurse with the education to the other workers at the department. This is described under the heading *'the education program'*.

#### Step 6 Evaluation of the implemented solutions

A third meeting is planned with the participants of the working group and the trained occupational nurse four to six weeks after meeting two. During this meeting the working group evaluates the implementation of the solutions. Further, the implementation status of the solutions (implemented, not implemented, in progress) is discussed. If needed solutions are adapted to better fit in the organisation.

#### Step 7 Maintenance

The solutions and recommendations will be given a permanent place in the department by using the Dermacoaches, by training new employees in using the recommendations, and by placing the topic on the agenda of meetings regularly during the year.

#### The education program

The goal of the education program is to inform all workers about the risk on hand eczema, the importance of preventive measures and to train them in actual use of individual preventive measures according to the NVAB-guideline, such as the use of hand alcohol, the use of protection measures - such as protective gloves in general and the use of cotton gloves worn underneath rubber and plastic gloves - and the use of recommended high fat skin care products. Most important is that the workers become aware of their own risk behaviour in relation to hand eczema and how to reduce this risk. They also receive information from the Dermacoach about the problems identified by the working group and the solutions for these problems.

The program is a short session (20 minutes) and is planned during a regular meeting of the workers at the department. The program is planned and carried out by the trained occupational nurse and the Dermacoach. More sessions are held to increase the reach of the education.

All workers participating at the session receive a bag containing products related to the prevention of hand eczema, like moisturizers and cotton under gloves. Afterwards, the Dermacoach will place key messages (reminders) at sinks or other relevant places at the department.

### Use of co-interventions

To our knowledge no specific program to prevent hand eczema are performed in the participating departments. However, co-interventions will be assessed in the questionnaire. In addition, department managers are asked whether there are other ongoing studies, planned re-organizations or other relevant changes at the department that can influence implementation. The necessity of knowing whether co-interventions took place is that the control group ideally does not receive any interventions during trial period and the intervention group does not receive any additional interventions. When this does occur the effect of the intervention can respectively fade or increase compared to the control group.

### Goal of the data collection

Eventually, this study will evaluate the procedures in two ways. The first is by performing a (cost-) effectiveness study relating the intervention to the prevention of hand eczema and, secondary, to the use of the recommendations. Considering this as an implementation study, it is important to evaluate the process as well. Therefore, a quantitative process evaluation is performed and in addition a qualitative exploration of barriers and facilitators related to the implementation of the recommendations.

### Data collection procedure

Departments can choose whether they want to receive the questionnaires online or by hard copy. The online questionnaires are sent to the workers by e-mail containing a link to the questionnaire. The hard copy questionnaires are sent to the department managers, who hand out the questionnaires to the workers. The researchers collect the completed questionnaires. Approximately one month before the start of the working groups the baseline questionnaire is sent to the workers. In order to enhance the response a maximum of three reminders will be send. Further, the department managers will be asked to encourage their workers to fill out the questionnaires. Subsequently, the researchers visit the departments before, during and after each measurement to encourage workers to fill out the questionnaires. In addition, incentives are used. This procedure has resulted in a inclusion rate of 60% and 20% dropout rate after inclusion in a comparable study to prevent back and neck pain in the target group in the VU University Medical Center [32].

### Outcome measures

#### Primary outcome measure

Primary outcome is defined as the frequency of (an episode of) eczema on hands or forearms within the past three months based on questions D1 ('Have you ever had hand eczema?'), D2 ('Have you ever had eczema on your wrists or forearms?'), and D5 ('When did you last have eczema on your hands, wrists and forearms?') in the Nordic Occupational Skin Questionnaire (NOSQ-2002) [33,34]. Question D5 is measured on a four-point scale containing the options: 'I have it just now', 'Not just now, but within the past 3 months', 'Between 3 - 12 months ago' and 'More than 12 months ago'. A dichotomous variable is created using these three questions for the prevalence of hand eczema in the past three months. An interval of three months is used, because hand eczema has an episodic and recurrent course.

#### Secondary outcome measures

The three questions from NOSQ-2002 only measure the presence or absence of hand eczema, without taking into account the symptoms related to it [33,34]. Therefore, a symptom-based questionnaire is added to measure the symptoms of hand eczema every three months [19].

The impact of hand eczema on the worker's disease-specific quality of life is measured using the DLQI [35]: a 10-item scale which measures the impact of skin diseases on several physical, psychological and social aspects of daily life. For this study we use the Dutch version of the DLQI adapted by Evers et al. [36]. It will be measured at baseline, after 6 and 12 months.

Workers' global assessment of the health of their hands and patients' global assessment of eczema will be assessed at baseline and after 6 and 12 months, using a 11-point Likert scale based on the NOSQ-2002 (question D12) [33].

Skin exposure during work time is measured using an adopted version of the NOSQ-2002 [33,34]. It will be measured at baseline and after 6 and 12 months.

The actual use of preventive measures is measured with a modified version of the NOSQ-2002. The modifications are necessary, because questions have to be in accordance with the specific work environment of the workers. Further, the researchers monitor whether the preventive measures are used or not. In addition to self reported use, information is collected at the department level about the actual use of protective measures like gloves, use of disinfectants and use of barrier creams. This information is gathered by the purchasing department and the pharmacy of the participating hospitals. Both the questions from the NOSQ-2002 and purchase data will be collected every 3 months.

Sick leave is measured by using the PRODISQ [37]: one general question on sick leave and three questions about sick leave due to hand eczema. Work productivity is measured using a single item question from the WHO Health Productivity Questionnaire [38,39] and three single item questions from PRODISQ [37]. All but one question on work productivity are measured on a 11-point Likert scale. Health care costs related to hand eczema are collected with respect to the economic evaluation. All these questions will be assessed every 3 months.

Several questions about the knowledge of prevention of hand eczema are included. Three questions are included asking whether the workers receive information about the prevention of hand eczema and what kind of information (e.g. leaflets, presentation) they receive. This is measured at baseline, after 6 and 12 months.

Psychosocial work characteristics will be measured at baseline and after 6 and 12 months by means of a Dutch version of Karasek's Job Content Questionnaire, containing the following constructs with a reliability between 0.65 and 0.83: decision authority and co-worker support [40]. Because the working groups in this study have to decide what measures they want to implement, it is important to know if there are possibilities for workers to take their own decisions. Therefore, we measure decision authority. Co-worker support is important, because we expect that colleagues have an influence on compliance to the recommendations.

It is known that the actual use of preventive measures for the prevention of musculoskeletal disorders is positively and significantly associated with behavioural change phases [41]. Therefore, the behavioural determinants attitude-social influence- self-efficacy (ASE) [42] for (the intention to perform) the desired behaviour - actual use of preventive measures - are asked using eight questions. This questions will be assessed at baseline, after 6 and 12 months.

#### Prognostic factors

At baseline sociodemographic data (i.e. age, gender, education, working hours per day, working days per week, nationality, job description) are assessed.

Several relevant questions on eczema are assessed at baseline, like eczema in the past - derived from the NOSQ-2002 [33,34] - and atopy [19]. Skin exposure during leisure time is measured on a Visual Analogue Scale (VAS). Questions on exposure in leisure time will be measured at baseline, after 6 and 12 months.

### Statistical analyses

All analyses are performed according to the intention to treat principle. Most analyses are performed at worker level. Two analyses are performed: 1) a crude analysis with the outcome variable measured at follow-up as the dependent variable adjusted for the outcome, measured at baseline, and 2) an analysis as above but adjusted for potential covariates (e.g. gender, age, type of work, history of hand eczema, and skin exposure). Effects of the intervention will be checked for effect modification (gender, type of exposure, number of preventive skin measures implemented). Generalised estimation equations (GEE) are used to analyse long-term results (i.e. 12 months after baseline). Furthermore, analyses at department level are performed by the use of multilevel analysis.

For all analyses a two-tailed significance level of < 0.05 is considered statistically significant. The multilevel statistical analyses are performed with MlwiN 2.0; linear and logistic regression analyses are performed with SPSS 15.0 (SPSS Inc. Chicago, Illinois, USA), and GEE analyses is performed with STATA version 7.0 (College Station, TX).

Considering the episodic nature of hand eczema, the use of transition models is necessary. In these models, the presence of hand eczema in the past three months is incorporated. The probability of getting hand eczema in workers with no hand eczema and the probability of getting no hand eczema in workers with hand eczema are modelled simultaneously by means of a logistic mixed model as is done in a study with a comparative design on low back and neck pain [32]. Transitions models will be conducted using the gllamm procedure in Stata version 10.0.

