## Methods/Design

### Study design

The Hands4U study is a two-armed randomised controlled trial (RCT). Randomisation is performed at the department level. Workers of the department allocated to the intervention group will receive the multifaceted implementation strategy (MIS); departments allocated to the control group will receive usual practice (no MIS). Data on all outcome measures are assessed at baseline, and 6 and 12 months after baseline. Data on the primary outcome measure (the frequency of (an episode of) eczema on the hands or forearms), as well as on adherence to the recommendations, sick leave, work productivity and health care costs are collected retrospectively every 3 months. The data collection started in April 2011.

The study protocol was approved by the Medical Ethics Committee of the VU University Medical Center. In this study, departments are included as a whole. Therefore, the Medical Ethics Committee decided that participants did not have to sign an informed consent.

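### Departments are randomised, but the worker-level effect tests as written carry no department term, and no analysis that accounts for department is named as primary

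*Protocol article*

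**What the plan says.** The unit of allocation is clear. Under Study design the article states "Randomisation is performed at the department level", and under Randomisation, stratification and blinding it repeats "Randomisation to the intervention group receiving the MIS or the control group takes place on the level of departments". The Sample size section says that clustered allocation has been allowed for and gives an intraclass correlation (ICC) of 0.73.

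The Statistical analyses section then sets out the following:

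- **Level:** "Most analyses are performed at worker level". Two models are described. The crude one adjusts for the baseline value of the outcome, and the second adds covariates.
- **Software for ordinary regression:** "linear and logistic regression analyses are performed with SPSS 15.0".
- **Multilevel:** "Furthermore, analyses at department level are performed by the use of multilevel analysis", run in separate software (MLwiN).
- **GEE:** used for the 12-month results, with no clustering unit given.
- **Transition models:** described as necessary because eczema is episodic, with onset and recovery "modelled simultaneously by means of a logistic mixed model" in gllamm. The level of the random effect is not stated.
- **Threshold:** "For all analyses a two-tailed significance level of < 0.05 is considered statistically significant".

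No sentence identifies a primary analysis, and none says that the worker-level tests account for department.

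**The concern.** When departments are allocated, the evidence about the intervention comes from comparing departments. Workers in one department share tasks, products and exposures. In the intervention arm they also share one working group, its chosen solutions, the role models and the education sessions. The article itself expects risk to differ between departments, since it stratifies on assessed risk.

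If outcomes within a department are positively correlated, a worker-level regression without a department term treats the workers as independent and reports standard errors that are too small. Its confidence intervals are too narrow, and a nominal 5% test rejects too often. This affects any worker-level effect test run that way, including secondary outcomes. Adjusting for baseline or worker covariates may reduce the residual correlation but does not replace a department term.

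The lack of a named primary analysis adds to the problem. If a worker-level regression and the multilevel model disagree, both are judged at the same threshold and the text does not say which one decides.

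**Working it through.** **Inputs from the article**

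- Sample size: 1200 workers to be analysed, 1500 recruited, 3000 invited, and 50 workers per average department.
- Participatory working groups: about 30 groups, one per intervention department.
- Statistical analyses: two-sided 0.05.

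**The plan's own counts**

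- 1200/0.80 = 1500 and 1500/0.50 = 3000, so the recruitment steps reproduce.
- 3000/50 = 60 departments, which agrees with about 30 in the intervention arm.
- Analysed workers per department: m = 1200/60 = 20.

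**Assumption**

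The article gives no credible department ICC, so 0.01, 0.02 and 0.05 are assumed values.

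**Formulas**

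- Design effect: DE = 1 + (m − 1) × ICC = 1 + 19 × ICC
- True standard error / reported standard error = √DE
- Actual two-sided error = 2 × [1 − Φ(1.96/√DE)]

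| Department ICC | DE | √DE | Actual error (formula) | Simulated, departments ignored |
|---|---|---|---|---|
| 0 | 1.00 | 1.00 | 5.0% | 5.0% |
| 0.01 | 1.19 | 1.09 | 7.2% | 7.2% |
| 0.02 | 1.38 | 1.17 | 9.5% | 9.2% |
| 0.05 | 1.95 | 1.40 | 16.0% | 15.9% |

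The stated 5% is reproduced only when the department ICC is zero. The simulation used 60 departments of 20 workers, a 24% rate, beta-binomial variation between departments and 20,000 runs. In the same simulated data, a test on department proportions stayed between 4.8% and 5.2%, so the excess comes from ignoring departments.

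**Sensitivity to cluster size**

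- m = 25 (1500/60): 7.8%, 10.7% and 18.6% at the three ICCs.
- m = 50: 10.8%, 16.4% and 29.1%.

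**The article's 0.73 as a department ICC**

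DE = 1 + 19 × 0.73 = 14.87, and the error is 2 × [1 − Φ(1.96/3.856)] = 61%.

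**GEE clustered on the worker only (conditional)**

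This takes the other reading of 0.73, as the correlation between one worker's measurements over four follow-up waves, and assumes that the department ICC is the same within and across waves. The variance factor for a worker's mean is (1 + 3 × 0.73)/4 = 0.7975. The ratio of true to reported variance is (0.7975 + 19 × ICC)/0.7975, which gives errors of about 8%, 11% and 19% at the three ICCs. The two readings of 0.73 are alternatives and cannot both apply.

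**The case against.** The strongest reply is that the article does not prove that the primary outcome will be tested wrongly.

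- **Transition model.** The section calls for a logistic mixed model for hand eczema in the past three months, which is the primary outcome. Such a model can carry a department random intercept. This stands: the primary outcome is not left to ordinary regression alone. But the stated reason for the model is the episodic course of eczema, and no department effect is mentioned.
- **GEE.** With the department as cluster and robust standard errors, GEE would be valid. This stands too. Silence on the cluster is not proof of error, and an article may leave such detail to a fuller document.
- **Meaning of worker level.** The phrase could name the unit of the outcome rather than a model that ignores departments, and the article does not say which outcomes go to SPSS. This has some force. Against it, worker-level and department-level analyses are listed as separate items, multilevel modelling has its own software, and nothing attaches a department term to the former.
- **Rank of the multilevel analysis.** One connecting word does not make it subordinate. That is fair, but nothing makes it the deciding test either.
- **Residual correlation.** Stratification by patient contact and risk, and adjustment for type of work and exposure, may lower the department ICC. They do not guarantee zero.

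A reader might infer that the trial has no valid test of its primary outcome, or that its error rate exceeds 60%. The documents support neither. The first is undecided in the text. The second needs 0.73 to be a department ICC, which is implausibly high and fits a within-worker correlation better.

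**Conclusion.** The point holds in limited form. The worker-level tests as described do not account for the unit of randomisation, yet they are judged at the same 0.05 as everything else. For the GEE and the transition model the role of department is unstated, not shown to be wrong. No analysis is designated primary, so the text does not secure a department-level basis for the main claim.

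For a single-wave worker-level test that ignores departments, the actual error is about 7% to 16% and standard errors are understated by 9% to 40%. These figures rest on about 20 analysed workers per department, equal department sizes and assumed ICCs of 0.01 to 0.05. The direction does not depend on the particular value: any positive residual department ICC puts the error above 5%. The 61% figure shows only what the article's own number implies at face value and is not a forecast.

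**What to change.** In the Statistical analyses section:

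1. Name one primary analysis of the primary outcome that includes department. Either a multilevel or transition logistic mixed model with a department random intercept (MLwiN or gllamm), or GEE clustered on department with robust standard errors, would do. No single model form is required.
2. Account for department in the same way in every worker-level secondary effect test.
3. Draw no significance claims from single-level regressions.

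The change is to wording. The software is already listed and data collection is unaffected. The cost is wider confidence intervals and somewhat lower power than the worker-level tests appear to give. At the assumed ICCs, 1200 workers carry the information of about 1200/1.19 = 1008, 1200/1.38 = 870 or 1200/1.95 = 615 independent workers. That loss comes from randomising departments; the change only makes the analysis report it.
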